The *Cyc*lical *L*ower Extremity *E*xercise for Parkinson’s (CYCLE) Trial is designed to test the hypothesis that FE and VE, while both aerobic, produce different clinical outcomes as a result of differential effects on the CNS. Specifically, the aims of the CYCLE trial are: 1) To determine the effects of FE and VE on motor function in individuals with PD; 2) To determine the effects of FE and VE on non-motor function in individuals with PD; and 3) To determine the pattern of magnetic resonance imaging (MRI) activation associated with FE and VE. It is hypothesized that FE will elicit significantly greater improvements in clinical and biomechanical measures of motor and non-motor performance when compared to voluntary and no-exercise control groups. Further, it is hypothesized that FE will elicit increased cerebral blood flow and cortical and subcortical activation following exercise, while voluntary and no-exercise groups will result in no change in the pattern or extent of activation as seen on neuroimaging.

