### Power analysis

For Aim 1, the UPDRS motor score will be the primary outcome. Our power analysis was calculated based on UPDRS motor data from our previous project comparing FE and VE interventions on UPDRS ratings. We observed a mean (95% confidence interval (CI)) reduction of -5.3 (-18.0, 7.4) in the FE group and 0.4 (-15.3, 16.1) in the VE group from baseline to end of treatment (EOT) at 8 weeks. This corresponds to a difference (improvement, reduction) in means (95% CI) of -4.9 (-20.6, 10.8), standard deviation (SD) of difference = 8.0, P = 0.004. Assuming similar variability for the current proposal, with N = 40 subjects per exercise group, we will be able to detect differences of 5.0 or more between groups on UPDRS with 90% power at the 0.05 significance level, adjusting for 3 group comparisons at each of EOT evaluations. No published data exists for outcomes in Aim 2 or 3 with respect to exercise and PD. In general, with 40 subjects per exercise group, power will be 99 percent to detect differences of 1.2 SDs or more between the groups. For Aims 1-2, comparisons at particular time points power is 90% to detect differences of 1.3 SD, applying a Bonferroni correction for analyzing time points (2 post-intervention times) individually. All calculations assume Tukey adjustment for comparing the 3 groups.

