### MRI data collection

For this study, structural MRI, functional MRI (fMRI), fcMRI and cerebral blood flow (CBF) data will be acquired on four occasions: Baseline (on and off antiparkinsonian medication), EOT, and EOT + 4 weeks. The structural scan is a T1-weighted anatomic image for identifying brain anatomy. The fMRI and fcMRI scans will be acquired with blood oxygen level-dependent (BOLD)-weighted echoplanar imaging scans. Two fcMRI scans will be acquired while subjects rest in the scanner with eyes closed. Two fMRI scans will be acquired in each session while subjects complete finger tapping in the following self-paced repeating sequence: digit 1, digit 3, digit 5, digit 2, digit 4 with each limb (left and right limbs, in random order) in a block paradigm (alternating 48 second-long blocks of tap and rest phases, repeated 4.5 times) to determine the relationship between changes in upper extremity motor performance and pattern of brain activation. Additional measures recorded for exploratory purposes include fcMRI between nodes of the putative motor network.

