### MRI data

Functional imaging data collected during the motor tasks will be retrospectively motion corrected with a slice-based second-order motion model [45,46] in parallel with physiologic noise regression [47], spatially filtered [48] and analyzed for task-related activation using a least-squares fit of the voxel-level BOLD signal to a reference function generated from the task design [49]. The result will be a whole brain map of Student’s t-values reflecting the response of each voxel for each task. A paired *t*-test of the total volume of activation above a t-value of 3.5 (p < 0.001, uncorrected) in the supplemental motor area will be calculated in all subjects. Correlation will be calculated between the change in activation volume of the supplemental motor area and subcortical structures of interest (globus pallidus, putamen, and thalamus) for each subject and the corresponding biomechanical measures during a finger tapping task during the scan and UPDRS rating.

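### The planned activation–motor correlation names no term for randomised arm, so as naturally read it mixes the treatment contrast with the brain–motor relationship it is meant to describe

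*Protocol article*

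**What the plan says.** The aim of the tapping scans, under MRI data collection, is "to determine the relationship between changes in upper extremity motor performance and pattern of brain activation".

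The MRI data section gives the analysis: "Correlation will be calculated between the change in activation volume of the supplemental motor area and subcortical structures of interest". The structures meant are the putamen, thalamus and globus pallidus, and the other side of the correlation is described thus: "for each subject and the corresponding biomechanical measures during a finger tapping task during the scan and UPDRS rating". The sentence before it describes a paired t-test of supplemental motor area volume, which "in the supplemental motor area will be calculated in all subjects". Neither sentence mentions an arm term, stratification or a within-arm analysis.

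No other section supplies one for this correlation. The group effect under Data analysis belongs to the repeated-measures ANCOVA for motor and non-motor outcomes. The arterial spin labeling section names basal cerebral blood flow as the only imaging adjustment.

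The Background states what the investigators expect of the two correlated variables. For activation under FE, "it is hypothesized that FE will elicit increased cerebral blood flow and cortical and subcortical activation following exercise". The remaining two arms are expected to differ from this, as the text goes on to say: "while voluntary and no-exercise groups will result in no change in the pattern or extent of activation". For function, the expectation again favours FE over both other arms: "It is hypothesized that FE will elicit significantly greater improvements in clinical and biomechanical measures of motor and non-motor performance".

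**The concern.** If both hypotheses hold, randomised arm shifts both variables. FE participants sit at higher activation change and better motor change; VE and control participants sit elsewhere on both axes. A correlation over all participants picks up that separation even when, among people given the same treatment, the size of the activation change says nothing about the size of the motor change.

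A significant result would then have two explanations that the statistic cannot separate: FE changed both measures, or activation change tracks motor change. The first is already addressed by comparing arms. Only the second adds information on mechanism, and this correlation is the only imaging-to-function analysis that the article specifies.

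**Working it through.** The article gives no sample size, effect size or power for this correlation, so there is no stated figure to reproduce.

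**Inputs from the article**
- N = 100, allocated 2:2:1, hence 40 FE, 40 VE and 20 control (Study design; Randomization).
- Significance level 0.05 (Data analysis), taken as two-sided.
- UPDRS shift in FE: 5.0 points, the detectable difference, over an SD of 8.0 (Power analysis). 5.0/8.0 = 0.625 SD.

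**Assumptions**
- Activation shift in FE of 0.3 to 1.2 SD. The article gives none.
- No shift in VE or control on either variable. The article says this for activation; for UPDRS it is my simplification.
- Zero correlation within every arm, normal changes with equal variances, and usable scans from all 100.

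**Expected pooled correlation.** Let p = 0.40 be the FE share, so p(1 − p) = 0.24, and let dU and dA be the standardised FE shifts. A fall in UPDRS is an improvement, hence the minus sign:

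r = −0.24 · dU · dA / √[(1 + 0.24·dU²)(1 + 0.24·dA²)]

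- dU = 0.625, dA = 0.3: numerator 0.24 × 0.625 × 0.3 = 0.0450; denominator √(1.0938 × 1.0216) = 1.057; r = −0.043.
- dU = 0.625, dA = 1.2: numerator 0.1800; denominator √(1.0938 × 1.3456) = 1.213; r = −0.148.

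**Rejection rate.** Simulated trials, at least 20,000 per scenario, comparing the Pearson test on all 100 (98 df) with the partial correlation given arm (96 df):

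| Activation shift (SD) | Pooled, VE unshifted | Pooled, VE at half of FE on both | Adjusted for arm |
|---|---|---|---|
| 0 | 5% | 5% | 5% |
| 0.3 | 7% | 6% | 5% |
| 0.5 | 11% | 7% | 5% |
| 0.8 | about 18% | 10% | 5% |
| 1.2 | about 31% | 15% | 5% |

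The arm-adjusted test keeps about 86% power for a true within-arm correlation of 0.3.

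**Sensitivity**
- Pilot arm means, "reduction of -5.3 (-18.0, 7.4) in the FE group and 0.4 (-15.3, 16.1) in the VE group": they differ by 5.7, and 5.7/8.0 = 0.71 SD. Pooled rates are then 8% to 39% for activation shifts of 0.3 to 1.2 SD. The 4.9 that the article gives as the difference (4.9/8.0 = 0.61 SD) returns 7% to 31%.
- Only 60 usable paired scans (assumed, 24/24/12): about 8% at an activation shift of 0.5 SD and 21% at 1.2 SD.
- Raw UPDRS score instead of change, with an assumed SD of 12 (5.0/12 = 0.42 SD): about 8% and 17% at the same two shifts.

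**The case against.** **Pooling is inferred.** The article never says in words that the arms are combined, and the all-subjects phrase belongs to the preceding t-test. A fuller plan could stratify. This stands as a limit: a reader might infer that the protocol commits to ignoring arm, and the text does not go that far. The article does, however, state the statistic, its unit and its variables, and nothing elsewhere in it brings arm into this analysis.

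**Total association is also a legitimate quantity.** The stated aim does not say within arm. If FE works through activation, the between-arm component is part of the relationship. The rates above are errors only against a within-arm null, since the total correlation in those simulated populations is truly non-zero. This is fair, and it is why the pooled value should be kept as description. It does not make the pooled value evidence on mechanism: a link between a possible mediator and the outcome has to be assessed given treatment. The within-arm association is itself not randomised, so it too supports only cautious statements.

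**The size can be exaggerated.** If both variables are shifted by 1.2 SD, the pooled rejection rate reaches 76%. That figure does not describe the UPDRS correlation. In the Power analysis, 1.2 SD is a difference detectable with high power, not an expected effect, and it is about twice the 0.625 SD implied for UPDRS.

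**The intended use can be exaggerated.** A reader might infer that the trial will present a significant correlation as proof of mechanism. The abstract's Discussion claims only that combining the outcomes may yield such insight, and no section commits to a mediation reading.

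**Conclusion.** The point holds as a minor improvement to a supportive Aim 3 analysis. As naturally read, the correlation mixes the between-arm difference with the within-arm brain–motor relationship. Under the trial's own hypotheses it can be significant when no within-arm link exists.

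The inflation is real but moderate: about 7% to 31% against a nominal 5%, with a spurious correlation of about 0.04 to 0.15 in absolute value, and 6% to 15% if VE moves half as far as FE. At the low end it is barely visible. These figures rest on assumed activation shifts, complete imaging in 100 participants, and UPDRS entering as change; fewer usable scans or a raw score would lower them. It would be wrong to infer that the trial's main conclusion is at risk, because the primary UPDRS comparison and the ANCOVA for motor and non-motor outcomes do not depend on this analysis.

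**What to change.** In the MRI data section, state that the correlation will be adjusted for randomised arm, either as a partial correlation or by regressing motor change on activation change plus two arm indicators. Report it with its 95% CI and base any mechanistic statement on that estimate. Show the pooled correlation alongside, labelled as descriptive. If the full plan already stratifies or adjusts by arm, one clarifying sentence is enough.

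The cost is that wording and two degrees of freedom (98 to 96 with complete data). No new data are needed.

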### Arterial spin labeling data and CBF measurement

Exercise may have an effect on baseline CBF. Basal CBF will affect the amplitude of the BOLD signal in response to a given neuronal activation level. In order to control for this possible confound to our measurement, we will measure basal CBF during each imaging session in order to 1) assess whether there are observed baseline CBF changes with the proposed exercise regimen, and 2) to permit the inclusion of this measure in a population analysis in order to control for this effect. A Q2TIPS arterial spin labeling (ASL) scan will be used to measure baseline CBF [50]. The ASL scan parameters are as follows: TE/TR/Flip = 2300/13/80, 12 axial slices 5mm thick, 1mm slice gap, FOV = 256x256, matrix = 64x64, TI1/TI2/SST = 700/1400/1100, bandwidth = 150kHz, repetitions = 139, Tag Slab = 100mm with 25mm gap.

### Adverse events

Serious adverse events, defined as an adverse experience that results in death, life-threatening experience, hospitalization, or significant disability, will be reported to the Cleveland Clinic Institutional Review Board within 10 working days. Non-serious adverse events will be reported annually. At the time of any adverse event, the event will be formally recorded by a member of the study team and reviewed by the primary investigator, who will determine if protocol or informed consent changes are necessary.

## Discussion

Although exercise prescription has become an increasing popular treatment for individuals with PD, there are currently no specific recommendations regarding mode, intensity, and duration [9]. In this protocol, we are prescribing a very specific mode, intensity, and duration of exercise with the hope of providing insight about exercise prescription. Specifically with aerobic exercise, it has been noted that there are gaps in literature on the immediate and long-term effects on PD symptoms [15]. Our follow-up periods include assessments up to 8 weeks following cessation of the intervention to determine the interim effects of this form of exercise.

While the UPDRS is a readily accepted outcome measure with PD; there is a lack of biomechanical outcome measures used in clinical trials for neurological populations. Through literature review, previous experience, and knowledge of the disease symptomology, the selected outcomes are comprehensive, objective, and systematic which will provide the opportunity to truly understand the clinical and behavioral effects of FE and VE on PD function. By automating several outcome measures to provide a more detailed and precise data collection tool, there is the potential for further understanding of PD symptomology. For example, in the Trail Making Test, the movement and dwell time can be separated, thus allowing the investigators to determine if time spent on a test is due to movement time, indicating a motor impairment, or dwell time, indicating a cognitive impairment from the individual processing which digit or number is next in the sequence. Likewise with the iPad version of the NHPT, the participant performs 2 different versions of the test (Figure 3). As a measure of in-hand manipulation, the first version consists of having the participant grasp, manipulate, and transfer the pegs from a dish to one of the 9 holes, remove the pegs, and return them to the dish. The second part of the test involves transferring pegs to and from a row, rather than the dish, to calculate transport time only. This differentiation between in-hand manipulation and transfer time could be helpful in differentiating between deficits.

Several of these iPad modules, including the postural sway test, NHPT, and Processing Speed Test, have been found to be reliable, sensitive, and clinically meaningful in individuals with multiple sclerosis [39]. This method of standardized testing, if found to be reliable and feasible in individuals with PD, will provide further evidence that objective, quantitative outcomes that can be used in both a research and a clinical setting are adventitious for neurological populations.

CYCLE Trial has the potential to make a unique contribution through the neuroimaging component. We have published researched that supports the benefit of a one-time bout of cycling on motor cortex functional connectivity; [23] however, the long-term effects of exercise on CNS connectivity is not known. By conducting imaging in various on and off-medication states at baseline, EOT, and EOT + 4 weeks, this study will provide insight into the potential neurophysiological CNS changes that exercise can produce in individuals with PD.

Overall we feel that the results of this study have the potential to directly impact patient care and will add to a body of evidence that challenges clinicians to view exercise as medicine for individuals with PD.

## Abbreviations

PD: Parkinson’s disease
CNS: Central nervous system
FE: Forced exercise
VE: Voluntary exercise
UPDRS: Unified Parkinson’s Disease Rating Scale
fcMRI: Functional connectivity Magnetic Resonance Imaging
CYCLE: Cyclical Lower Extremity Exercise for Parkinson’s disease
CI: Confidence interval
EOT: End of treatment
SD: Standard deviation
CPX: Cardiopulmonary exercise testing
HR: Heart rate
MRI: Magnetic Resonance Imaging
PDQ-39: Parkinson’s Disease Questionnaire-39
UPSIT: University of Pennsylvania Smell Identification Test
BDI-II: Beck Depression Inventory II
NHPT: Nine Hole Peg Test
fMRI: Functional Magnetic Resonance Imaging
CBF: Cerebral blood flow
BOLD: Blood oxygen level-dependent LEDD, levodopa equivalent daily dose
VO_2_: Volume of oxygen uptake
ALS: Arterial spin labeling
